# A protocol of a pilot randomised trial (Action-RESPOND) to support rural and regional communities with implementing community-based systems thinking obesity prevention initiatives

**DOI:** 10.1371/journal.pone.0302047

**Published:** 2024-05-02

## Abstract

**Background:**

Over a quarter of children aged 2–17 years living in Australia are overweight or obese, with a higher prevalence reported in regional and remote communities. Systems thinking approaches that seek to support communities to generate and implement locally appropriate solutions targeting intertwined environmental, political, sociocultural, and individual determinants of obesity have the potential to ameliorate this. There have however been reported challenges with implementation of such initiatives, which may be strengthened by incorporating implementation science methods.

**Methods:**

This pilot randomised controlled trial protocol outlines the development and proposed evaluation of a multicomponent implementation strategy (Action-RESPOND). to increase the implementation of community-based systems thinking child obesity prevention initiatives The target of this intervention is ten rural and regional communities (or local government areas as the unit of allocation) within Northeast Victoria who were participants in a whole-of-systems intervention (RESPOND). Action-RESPOND builds on this intervention by assessing the impact of offering additional implementation strategies to five communities relative to usual care. The development of the multicomponent implementation strategy was informed by the Promoting Action on Research Implementation in Health Services (PARIHS) framework and consists of seven implementation strategies primarily delivered via ‘facilitation’ methods. Implementation strategies aimed to ensure initiatives implemented are i) evidence-based, ii) address community’s specific needs and iii) are suitable for local context. Strategies also aimed to increase the community’s capacity to implement, through iv) improving the health promotion team’s implementation knowledge and skills, fostering v) leadership, vi) physical resources and vii) community culture to drive implementation. The feasibility, acceptability, potential impact, and cost of the strategy will be assessed at baseline and follow up using surveys administered to key representatives within the community and internal records maintained by the research team.

**Discussion:**

By leveraging an existing community-based whole-of-systems intervention, Action-RESPOND offers a unique opportunity to collect pilot feasibility and early empirical data on how to apply implementation and systems science approaches to support obesity prevention in rural and regional communities in Victoria.

## Introduction

Childhood obesity is one of the most significant global population health challenges, as it increases children’s risk of developing type 2 diabetes, cardiovascular diseases, and liver complications, during their childhood as well as their adulthood [1]. The World Health Organisation estimated that over 39 million children under five and 340 million children aged 5–19 years were overweight or obese in 2016 [2]. In Australia, over 25% of children aged 2–17 years are overweight or obese [3], with rates being disproportionately higher among those living in regional and remote areas [4, 5]. Medical costs related to obesity in children aged 6–13 years are estimated at $ AUD 43 million annually in Australia [6]. It is well established that obesity is caused by a range of environmental and individual determinants that interact in complex systems [7, 8]. For example, broader environmental determinants such as a lack of play spaces or walking paths is likely to reduce an individual’s motivation to engage in physical movement and activity, while availability and marketing of ‘less healthy’ foods could result in poor dietary choices [1].

To date however, much of the empirical research aiming to prevent childhood obesity focuses on interventions that target individuals or single settings. Systematic reviews of interventions targeting single settings, such as schools and childcare centres, show that they can improve dietary outcomes, physical activity and prevent excessive weight gain [9–11], however the effects of these interventions are often small and attenuate when delivered at scale. Reviews of randomised controlled trials (RCTs) of nutrition, physical activity, and obesity prevention interventions report that these interventions retain less than 50% of the effect when scaled up [12–14]. This may be because interventions are often developed and tested in controlled research environments and therefore when scaled up, require adaptation to ensure fit within the real-world context. As such, these interventions do not maintain the same fidelity and dose when scaled up, contributing to the attenuation in effect.

To address such challenges, population-level interventions that move beyond individual interventions and focus on establishing partnerships and systems, which lend themselves to ongoing and sustained lifestyle and environmental changes, are needed to meaningfully prevent obesity [15]. The "Shape Up Somerville" program in Massachusetts (USA) is one such example of where community-based systems level changes has produced meaningful changes over time [16]. This program involved collaboration between government agencies, schools, local businesses, and community organizations to implement multi-level interventions targeting nutrition, physical activity, and built environment changes between 2003 and 2005. This program produced positive changes on child and parent BMI post intervention with an estimated $197,120 USD net benefits over 10-years. The authors postulated that this positive outcome, which extended beyond improvement to individual children’s health, was made possible by the community-wide, systems-based nature of the interventions [16]. Indeed, engaging with these systems forms a key focus of obesity prevention strategies for countries including Australia and the UK [17, 18].

Systems thinking encompasses concepts, principles, and methodologies which allow us to understand, analyse, and address complex problems by considering them as interconnected, dynamic systems rather than isolated components [15]. Some of the key components of systems thinking include feedback loops (i.e. where an action is implemented in the system, and the system responds in a way that either reinforces the initial action taken or pushes back against the initial action), emergent properties (i.e. systems can exhibit emergent properties that arise from interactions and relationships), non-linear causality and dynamic behaviour [19]. A systematic review and meta-analysis found that using system science methods in health service design and delivery significantly improved both patient outcomes (n = 14 studies, OR = 0.52 (95% CI 0.38 to 0.71) I^2^ = 91%) and service outcomes (n = 18 studies, OR = 0.40 (95% CI 0.31 to 0.52) I2 = 97%) [20]. A narrative review of 65 articles (33 addressing obesity) reported that interventions which incorporated systems science methods resulted in a range of positive health outcomes, although the two good quality no RCTs found mixed effects on health and wellbeing outcomes [21]. Despite the promise of such interventions, there have been well-documented challenges and variability with the implementation of actions arising from these methods [22–24].

In childhood obesity prevention, the Whole of Systems Trial of Prevention Strategies for Childhood Obesity intervention (the WHO STOPS trial) applied a group model building (GMB) process to generate an agreed systems map of childhood obesity causes for a community, and in doing so, identified intervention opportunities through leveraging the dynamic aspects of the system [25]. GMB is a participatory approach grounded in systems thinking and involves a structured process where a diverse group of stakeholders collaboratively create a visual map, to build a shared understanding of the problem and develop community-led, locally tailored solutions [26, 27]. The WHO STOPS trial resulted in reductions in prevalence of overweight/obesity in the first two years of the intervention, however, was not sustained at four-year follow up; due in part to varying intensity of implementation [28]. The Lancet Commission on Obesity noted that inconsistent implementation constrains the effectiveness of community-developed interventions, pointing to the need for a greater application of implementation science to help overcome these barriers [29].

Implementation science [30] provides evidence-based tools, methods, and frameworks to support the design of a more systematic approach to implementation [30] of community-developed, systems thinking-based initiatives. In particular, implementation science draws on empirically-developed frameworks to guide the systematic planning, implementation and evaluation of complex interventions. For example, frameworks such as the Consolidated Framework of Implementation Research [31] and the Theoretical Domains Frameworks [32] have been widely used to systematically identify barriers to implementation and support the selection of evidence-based implementation strategies to improve implementation processes [33]. Intentionally embedding such methods into systems thinking approaches could provide deeper understanding into implementation context, drivers of change and help to systematically consider the evolving nature of the EBI knowledge users, systems, and organisations within community-based systems approaches [34]. A recent systematic review however, identified just 14 studies that have described the simultaneous use of implementation science and systems science in population health prevention interventions [35]. Of these, few explicitly explored how to apply implementation science to systems thinking approaches, and none explicitly examined how these two sciences could be best utilised together.

Therefore, we sought to undertake a pilot study to describe the potential usefulness of applying implementation science and systems science methods to support delivery of actions generated as part of GMB processes.

Specifically, this pilot RCT aims to:

understand the potential impact of implementation strategies on fidelity of implementation;assess acceptability and feasibility of the implementation strategies;assess the determinants (barriers and facilitators) related to implementation of identified actions;document adaptations made to actions in the process of implementation; andquantify the resources required to deliver implementation strategies; and to plan and implement an identified action arising from a participatory community-based systems thinking process (i.e. the GMB process).

## Materials and methods

### Context and setting

This pilot study builds on the Reflexive Evidence and Systems interventions to Prevent Obesity and Non-communicable Disease (RESPOND) study. RESPOND was a cluster randomised controlled trial (cRCT) undertaken with ten rural and regional communities located within the Ovens Murray and Goulburn Valley regions of Northeast Victoria, Australia [36]. Rural and regional classifications were based of that specified by the Victorian Department of Health [37] which is based on the Australian Statistical Geography Standard Remoteness Structure. For this trial, communities were the unit of analysis and defined by local government area (LGA) boundaries, which represent geographical divisions administered by municipal governments within Australian states. RESPOND employed systems thinking approaches in the design, implementation, and evaluation of a community-developed intervention to prevent obesity among children aged 0–12 years.

Five communities were randomised to receive RESPOND and five to a wait-list control. The methods for this study have been described in detail elsewhere [36] and the intervention included: i) establishment of strong governance with key partners (including Beechworth Health Service, Central Hume Primary Care Partnership, Gateway Health, Goulburn Valley Primary Care Partnership, Greater Shepparton City Council, Lower Hume Primary Care Partnership, Numurkah District Health, Upper Hume Primary Care Partnership, VicHealth, the Victorian Department of Education and Training, the Victorian Department of Health and Human Services and Yarrawonga Health), and clearly define roles and responsibilities; ii) routine childhood obesity and risk factor monitoring to support outcome assessment; and iii) capacity building to the communities in systems science methods, notably facilitating participatory systems mapping methods (i.e. the GMB processes) and iv) implementation of actions. All ten communities received the RESPOND program between 2020–2023. The delivery of the RESPOND program coincided with significant disruptions due to COVID-19 and bush fires in the region, significantly impacting on organisational priorities, loss of momentum of implementation, and redeployment of human resources [24].

### Trial design

This pilot RCT (called Action-RESPOND) seeks to build on some of the implementation challenges faced in RESPOND by systematically developing an enhanced implementation support package and assessing the feasibility and potential impact of this with the ten communities already participating in RESPOND. Five communities will receive a multicomponent implementation strategy (intervention) and five will not receive any additional implementation support (control). The trial will assess data at baseline and approximately 9-months follow up (see Fig 1). The reporting of this protocol was consistent with the CONSORT-pilot RCT guidance [38] and the Standards for Reporting Implementation Studies (STARI) statement [39]. Data collection for this trial began in June 2023.

**Fig 1 pone.0302047.g001:**
[figure not shown]
Schedule of enrolment, intervention and assessments for the Action-RESPOND pilot RCT as outlined in the SPIRIT recommendations [39].

### Ethics

This study has received ethical approval from Deakin University Human Research Ethics Committee (HEAG-H 12_2019). Written informed consent will be obtained from all participants prior to each data collection activity (via an online consent form prior to the survey or during attendance at the GMB workshops by a member of the research team).

### Eligibility criteria

The overall inclusion criteria for this study is at the ’community’ level (i.e. LGAs in Victoria). Communities that are included within the geographical area considered as rural/regional and have agreed to participate in the larger RESPOND Trial will be invited to participate. Ten LGAs in Victoria are included.

The backbone team from each LGA form the main participants in the current study. Recruitment of the LGAs and backbone team members were undertaken as part of the larger RESPOND Trial. For members to be part of the current study, they need to have some formal role in implementation (and could report on extent of implementation) and are located in the target LGAs.

### Randomisation

Randomisation occurred at the level of whole communities (LGAs) as part of the larger RESPOND trial and was conducted by a statistician with no knowledge of the communities. Ten LGAs were ranked in order of population size and divided into five pairs. A computer-generated random list was created by a study statistician who was not involved in the enrolment procedures. One community from each pair received either Action-RESPOND or usual care using a random list generated by the study statistician.

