### 1. Generation and provision of evidence-briefs and local data

Following GMB3, a presentation of the evidence for the actions that have emerged will be provided by the research team. This will be accompanied by local data on potential reach of such actions and the extent of local implementation where available. This will be briefly presented at an online meeting and a discussion around the actions (GMB3 debrief), facilitated by a member of the research team. Additionally, prior to the Edu Workshop, a recorded PowerPoint presentation summarising reviews on effectiveness of community-based childhood obesity prevention interventions are circulated to the backbone team of each community.

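### The Randomisation section places the Action-RESPOND allocation inside the RESPOND randomisation, which had different arms, so it is unclear what the fidelity and adoption contrast compares

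*Protocol article*

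**What the plan says.** Under Context and setting, the protocol article describes the parent trial in ten LGAs: "Five communities were randomised to receive RESPOND and five to a wait-list control". It adds: "All ten communities received the RESPOND program between 2020–2023". No start dates are given by arm.

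Under Randomisation, the only account of allocation for Action-RESPOND, it says: "Randomisation occurred at the level of whole communities (LGAs) as part of the larger RESPOND trial". The procedure follows: "Ten LGAs were ranked in order of population size and divided into five pairs", and then "One community from each pair received either Action-RESPOND or usual care using a random list generated by the study statistician". No second randomisation is described or dated, and nothing maps the Action-RESPOND arms to the RESPOND and wait-list arms.

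Trial design gives five communities per arm among the ten already in RESPOND, with data collection from June 2023. The first strategy is tied to the end of the RESPOND workshops: "Following GMB3, a presentation of the evidence for the actions that have emerged will be provided by the research team".

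Under Data analysis, summed fidelity and adoption scores are compared between groups by linear regression with the baseline score as the only stated adjustment.

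**The concern.** The two sections cannot both be right as written. The RESPOND randomisation, as Context and setting describes it, allocated RESPOND or wait-list. It did not allocate Action-RESPOND or usual care.

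If its list was carried over, every Action-RESPOND community differs from every control in its RESPOND arm, and so in when it was scheduled to receive RESPOND. A difference in fidelity or adoption at about nine months could then reflect Action-RESPOND, the stage reached in RESPOND, or both. If a new list was drawn, the contrast is sound but the section misreports how the arms arose.

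The impact of the strategies on fidelity is the first aim in the Introduction, and fidelity and adoption data feed the decision on a fully powered trial under Progression criteria. A pilot need not be powered, but its reader must know what was randomised.

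**Working it through.** The article gives no sample size, power or alpha figure to reproduce. The check sets the sections side by side and then asks what the stated regression can estimate under each reading.

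**Inputs**
- 10 LGAs in 5 pairs by population size (Randomisation).
- RESPOND arms 5 and 5 (Context and setting).
- Action-RESPOND arms 5 and 5 (Trial design).
- One representative per community reports fidelity and adoption, so there are 10 observations (Fidelity and adoption of action implementation).
- Regression on arm and baseline score (Data analysis).
- Assumption for step 3 only: a new draw would have used the same five pairs.

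**Step 1: the text.** Randomisation places the draw within RESPOND and gives it the arms Action-RESPOND and usual care. Context and setting gives the RESPOND draw the arms RESPOND and wait-list. Eligibility criteria uses the same expression about the larger trial for recruitment, where it refers to the original RESPOND process. That favours the literal reading but does not prove it.

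**Step 2: list re-used.** Let A = 1 for Action-RESPOND, R = 1 for the original RESPOND arm and X = the baseline score. Suppose follow-up is Y = a + bX + dA + gR + error, where g is the effect of RESPOND timing.
- With 5 and 5 in each, corr(A, R) = (mean of AR - 0.25) / 0.25.
- Same list, R = A: (0.5 - 0.25) / 0.25 = +1. The stated regression's coefficient on A estimates d + g.
- Reversed list, R = 1 - A: (0 - 0.25) / 0.25 = -1. The coefficient on A estimates d - g.
- In both cases the four columns (intercept, X, A, R) have rank 3, so d and g cannot be estimated separately.
- Adjusting for X removes differences in starting level. It does not remove a different later course linked to RESPOND timing.

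**Step 3: new list drawn within the same pairs.** There are 2^5 = 32 possible allocations. The number of Action-RESPOND communities that were also in the original RESPOND arm is distributed as follows:

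| Overlap | 0 | 1 | 2 | 3 | 4 | 5 |
|---|---|---|---|---|---|---|
| Allocations | 1 | 5 | 10 | 10 | 5 | 1 |

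- Overlap 0 (reversed) and overlap 5 (identical) are fully confounded: 2/32 = 6.25%.
- In the other 30/32 = 93.75% the matrix has rank 4 and both effects can be estimated.
- Residual degrees of freedom: 10 - 3 = 7 for the stated model, and 10 - 4 = 6 with the RESPOND arm added.

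**Step 4: timing clues.** The first strategy follows GMB3, and section 7 (Inform and engage leadership) speaks of inviting managers to the workshops in the future tense, while data collection began in June 2023. This fits intervention communities that were still in the RESPOND workshops. It is only suggestive, because no GMB3 or start dates are given by arm.

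**The case against.** The strongest reply is that re-use is an inference. The last sentence of Randomisation names the Action-RESPOND arms, and being part of RESPOND may loosely mean nested among its communities. The section refers to a random list twice with the indefinite article, and describes the statistician in two ways, so more than one list is possible. The schedule figure is not visible here, and RESPOND's methods are reported elsewhere. This stands: confounding is possible but not shown. It does not remove the conflict, because under the nested reading the opening sentence is still wrong.

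A reader might infer more than the article supports:
- That COVID-19 and bushfire disruption fell mainly on early communities. Context and setting says only that delivery of RESPOND coincided with it.
- That controls entered baseline long after their own GMB3, or about three years later. The 2020–2023 window covers all ten communities and gives no gap between arms.
- That re-use would leave no randomised answer. It would still be a randomised contrast, but of a compound exposure; what is lost is attribution to Action-RESPOND alone.
- That communities knew their Action-RESPOND arm before baseline. Nothing says so.
- That the original RESPOND arm must be a covariate after a new draw. Random allocation does not require it.

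The pilot setting also limits the harm. Acceptability, appropriateness, determinants and adaptations are measured in intervention communities only. The specific progression criterion concerns acceptability, feasibility and likely adoption by over half the communities offered the programme, and does not rest on the between-group regression.

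**Conclusion.** The concern holds as a stated conflict with a conditional consequence. Taken literally, Randomisation makes the Action-RESPOND arm identical to the RESPOND arm or its reverse (correlation +1 or -1, rank 3 of 4). The fidelity and adoption comparison is then a randomised contrast of Action-RESPOND combined with RESPOND timing, and baseline adjustment cannot separate the two. If a new list was drawn, the section describes the wrong randomisation, and under the same-pairs assumption complete confounding would be a 6.25% chance.

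The article does not settle which case holds. Neither the size nor the direction of any bias can be given, because RESPOND dates by arm are not stated. Because the article states the allocation and states it inconsistently, this is not detail left to an analysis plan.

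**What to change.** State which list, drawn on which date, fixed the Action-RESPOND arms. Add a table of Action-RESPOND arm by original RESPOND arm, with months from GMB3 to baseline for each LGA.

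- **If the RESPOND list was re-used:** define the contrast as Action-RESPOND combined with RESPOND timing. Do not attribute the between-group difference in fidelity or adoption to Action-RESPOND alone, and carry that limit into the progression decision.
- **If a new list was drawn:** correct the Randomisation section. Adjustment for the original RESPOND arm is then optional, for example as a sensitivity analysis, and costs 1 of the 7 residual degrees of freedom. It is possible unless the new list happens to match or reverse the old one.

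The cost is a wording change and one extra table, plus a narrower claim if the list was re-used.
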